### Health care professional

We will send a Case Report Form (CRF) to the participant’s obstetric caregiver, either a midwife or a gynaecologist, to request information about the pregnancy and delivery. Complications during pregnancy and delivery, such as hypertensive disorders or pregnancy, foetal growth retardation, preterm labour, induced labour and caesarean section will be registered as well as information about the neonate (e.g., Apgar scores, birth weight, congenital malformations and admission to paediatric ward).

### Child

At 12 weeks postpartum we will perform a General Movements (GM) assessment by taking video recordings at home [63]. This assessment method evaluates the function of the young nervous system.

GMs are spontaneous movements that are present from early foetal life onwards until the end of the first half-year of life. GMs are complex, occur frequently and last long enough to be observed properly. If the nervous system is impaired, GMs lose their complex and variable character and become monotonous and poor [64].

For mapping of the SSRI exposure of the newborn, samples of meconium and breast milk (if breastfeeding) will be collected. SSRI in meconium will be measured by a validated method according to LCH guidelines on LC-MS/MS [65]. If feasible, hair strands and a buccal swab of the newborn will be collected at 12 weeks after birth (T6).

Long-term follow-up includes the well-established, reliable and valid Child Behaviour Check List 1.5-5 years, including the Caregiver Teacher Report Form (C-TRF) and the Language Development Survey (LDS) at 18 months postpartum [66]. Also, permission will be asked to obtain routine data from Centres for Childhood (CJG) until 24 months (in particular on length gain, weight gain, normal development, and any information on abnormal behavioural development).

### Sample size

Sample size calculation is based on the main aim of this study, which is to demonstrate non-inferiority of preventive CT with guided discontinuation of SSRIs (STOP) compared to continuation (GO), with respect to relapse or recurrence of a depressive episode up to 3 months postnatal. We will use a non-inferiority margin (tolerance threshold, ‘delta’) of 15 %. This is based on the assumption that this excess relapse (taking into account the possibility of restoring SSRI treatment) is still in balance with the expected beneficial effects of discontinuation of SSRI for the remaining mothers. We also anticipate that this balance is acceptable for women.

With this non-inferiority margin, and the assumption that the overall absolute risk of relapse will be around 15 % [67], we need 178 women, given alpha .025, power 80 %, and a one-sided test. To account for some attrition, we aim to include 200 women in total. Given this sample size, we have sufficient power to demonstrate small to moderate effect sizes of .42 or over on continuous secondary outcomes. With respect to dichotomous secondary outcomes, we will be able to detect odds ratios of 1.5 or over when the base probability is .5.

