### Statistical analysis

Analysis will primarily be carried out according to the intention-to-treat principle, i.e., the participants will be analysed according to their randomized allocation, regardless of the actual interventions received by the participant. Supplementary, we will perform analyses per protocol, i.e., according to actual SSRI use, irrespective of randomized arm.

The primary outcome, risk (cumulative incidence up to 3 months postnatal) of relapse of depression, will be compared between the randomized groups. Differences will be assessed statistically using a one-sided Chi-Square Test at a significance level of .025 and will be presented as a risk difference. The remainder of statistical tests will be performed two-sided at a significance level of .05.

Time to relapse will be compared between the randomized groups using survival analysis. Kaplan-Meier curves will be constructed and differences will be tested using the log-rank test. A Cox proportional hazard model will be used to calculate hazard ratios

Continuous outcomes, e.g., the General Movements scores at 3 months, will be compared between the groups using the unpaired *t*-test. Categorical secondary outcomes, e.g., obstetric complications, will be tested using Chi-Square Tests. For the continuous variables and categorical variables that are assessed more than twice, we will deploy linear mixed models and generalized linear mixed models respectively. These models use all available data (do not exclude persons with missing values) under the assumption of data being missing at random, and account for within-subject correlation over time. If despite randomization prognostically important factors differ between the groups, they will be adjusted for in supplemental analyses by including these factors in the pertaining regression models.

Subgroup analyses will be undertaken according to: Dutch/non-Dutch, nulliparous/multiparous, yes/no history depressive disorder and/or anxiety disorder, yes/no co-morbid anxiety symptoms or disorder. All effect parameters will be supplied with a 95 % confidence interval.

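### The claimed ability to detect odds ratios of 1.5 on dichotomous secondary outcomes is wrong: power for that effect is about 27% to 31%, and the detectable odds ratio is about 2.3 to 2.4

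*Protocol article*

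**What the plan says.** The Sample size section derives the trial size from the primary outcome: "we need 178 women, given alpha .025, power 80 %, and a one-sided test". It then adds a margin for dropout: "To account for some attrition, we aim to include 200 women in total". With that size it makes two claims about secondary outcomes. For continuous ones, "we have sufficient power to demonstrate small to moderate effect sizes of .42 or over on continuous secondary outcomes". For dichotomous ones, "we will be able to detect odds ratios of 1.5 or over when the base probability is .5".

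The Randomisation section gives 1:1 allocation, so the arms hold 89 women each (the number needed) or 100 each (the number recruited). The Statistical analysis section fixes the test for such outcomes: "Categorical secondary outcomes, e.g., obstetric complications, will be tested using Chi-Square Tests". It also fixes the error rate for everything but the primary comparison: "The remainder of statistical tests will be performed two-sided at a significance level of .05".

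**The concern.** At a base probability of one half, an odds ratio of 1.5 is a difference of only ten percentage points. A two-arm trial of 178 to 200 women looks several times too small to find that reliably, so the sentence appears to credit the design with a sensitivity it does not have.

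Much of the trial's secondary purpose rests on outcomes of this kind. The section on the health care professional lists complications of pregnancy and delivery, congenital malformations and paediatric admission. The Trial objectives state an expectation that tapering is better for child development. A reader who believes the trial can see an odds ratio of 1.5 may take a non-significant result on these outcomes as evidence that no effect of that size exists, in either direction.

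**Working it through.** **Inputs.** Base probability .5 and odds ratio 1.5 (Sample size). Arms of 89 or 100 (Sample size, Randomisation). Chi-square test, two-sided .05 (Statistical analysis). Power of 80% is stated for the primary outcome only and is taken here for secondary outcomes too; step 1 tests that assumption. Normal quantiles: 1.960 for two-sided .05 and 0.842 for 80% power, sum 2.802.

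**Step 1: reproduce the two neighbouring figures.**

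- Primary outcome, risk 15% in both arms, margin 15 points: n per arm = 2.802² × 2 × .15 × .85 / .15² = 88.95, so 89 per arm and 178 in total. This matches.
- Continuous secondary outcomes: d = 2.802 × √(2/89) = .420. This matches at 89 per arm, two-sided .05 and 80% power.

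The same convention should therefore lie behind the odds-ratio sentence.

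**Step 2: translate the odds ratio.** p2 = (.5 × 1.5) / (.5 + .5 × 1.5) = .75/1.25 = .60. The contrast is 50% versus 60%, with mean p̄ = .55.

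**Step 3: power for that contrast.** With the pooled variance under the null hypothesis,

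power = Φ{ [ |p2 − p1| √n − 1.960 √(2p̄(1 − p̄)) ] / √(p1(1 − p1) + p2(1 − p2)) }.

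Here 1.960 × √.495 = 1.379 and √(.25 + .24) = .700.

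- n = 89: Φ[(.943 − 1.379)/.700] = Φ(−.622) = 26.7%.
- n = 100: Φ[(1.000 − 1.379)/.700] = Φ(−.541) = 29.4%.

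Exact binomial power of the Pearson chi-square test is 26.9% and 31.0%.

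**Step 4: sample size needed.** n per arm = (1.379 + .842 × .700)² / .10² = (1.379 + .589)² / .01 = 387.3, so 388 per arm and 776 in total (816 with continuity correction). That is 776/200 = 3.9 times the recruitment target and 776/178 = 4.4 times the number needed.

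**Step 5: what the trial can detect with 80% power.** Solving the formula in step 3 for the odds ratio:

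| Per arm | Base .50 | Base .10 (assumed) |
|---|---|---|
| 89 | 2.38 (50% vs 70.4%) | 3.17 (10% vs 26.0%) |
| 100 | 2.26 (50% vs 69.3%) | 2.99 (10% vs 25.0%) |

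The 10% base is an illustration for a less common complication; the protocol gives no base rates for these outcomes.

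**Step 6: other readings of the sentence, at 80% power unless stated.**

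- One-sided .05: detectable odds ratio 2.15 (89 per arm) and 2.05 (100 per arm).
- Continuity correction: 2.51 and 2.36.
- Probabilities placed symmetrically about .5: 2.33 and 2.22.
- Total mistaken for the arm size: 1.83 (178 per arm) and 1.77 (200 per arm).
- Power of only 50%: 1.82 and 1.76.
- 1.5 meant as a risk ratio (50% vs 75%): power 94% and 96%, so 1.5 is not the detectable limit on that reading either.

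No single departure gives 1.5. Stacked departures can approach it (200 per arm with one-sided .10 gives 1.53), but they describe neither this trial's size nor its test.

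One formula does give the figure: logistic regression on a continuous standardized predictor, where the detectable log odds ratio per standard deviation is 2.802/√(N × .25). For N = 178 this is .420, and exp(.420) = 1.52; for N = 200 the odds ratio is 1.49. This may be the origin of the number, but the document does not say so, and it is not a comparison of two randomized arms.

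**Step 7: consistency of the two claims.** On the usual logistic conversion, d = .42 corresponds to exp(.42 × π/√3) = 2.14. A yes/no outcome carries less information than a continuous one, so its detectable odds ratio should be at or above that value. The corrected 2.26 to 2.38 is; 1.5 is not.

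**The case against.** The arithmetic is not in dispute. The strongest case on the other side is that the error does little harm, and that the reading rests on assumptions.

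- **Nothing depends on the figure.** The trial size comes from the primary outcome and reproduces; no test, threshold or decision rule uses the odds ratio of 1.5. This stands and limits the consequence to the interpretation of secondary outcomes.
- **The margin is not argued from child outcomes.** The Sample size section weighs the 15-point excess against benefits of discontinuation for the remaining mothers, and acceptability to women. This stands: the error does not undermine the stated rationale for the margin.
- **Confidence intervals are already promised for all effects.** True, and they help. But if both arms showed exactly 50%, the 95% interval with 100 per arm would be exp(±1.96 × √(4/50)), or 0.57 to 1.74. With 89 per arm, √(4/44.5) gives 0.56 to 1.80. A perfectly null result would still leave 1.5 inside the interval, in conflict with what the protocol tells the reader to expect.
- **80% power is inferred for secondary outcomes.** True, but the effect size of .42 reproduces under it, and power of 27% to 31% does not amount to being able to detect an effect by any usual standard.
- **Mixed models for repeated categorical outcomes could add power.** They apply only to variables assessed more than twice. A 3.9- to 4.4-fold gain over five occasions needs a within-woman correlation of (5/3.88 − 1)/4 = .07 down to (5/4.36 − 1)/4 = .04, which the protocol does not assume. Outcomes recorded once, such as delivery complications, gain nothing.
- **The logistic conversion in step 7 is approximate.** It is, and the conclusion does not need it.

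**Conclusion.** The statement is wrong as written. For the two-arm comparison the protocol plans, power to detect an odds ratio of 1.5 at a base probability of .5 is 26.7% to 29.4% by the normal approximation and 26.9% to 31.0% exactly. The detectable odds ratio at 80% power is 2.38 with 89 per arm and 2.26 with 100 per arm. The claimed effect would need about four times the planned sample. For outcomes with a base risk well below one half the detectable odds ratio is larger still, about 3.0 to 3.2 at an assumed 10%.

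The conclusion rests on 1:1 allocation, a two-sided chi-square test at .05 and an 80% power target. The first two are stated; the third is inferred from the neighbouring effect size. The primary sample size and the figure of .42 are both sound.

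**What to change.** Replace the sentence on dichotomous outcomes with one along these lines: for dichotomous secondary outcomes the trial has 80% power (two-sided .05) to detect odds ratios of about 2.3 (100 per arm) to 2.4 (89 per arm) when the base probability is .5, that is, 50% versus about 70%; at an assumed base probability of .10 the corresponding odds ratios are about 3.0 to 3.2. State the 80% power explicitly for secondary outcomes. If 1.5 was meant per standard deviation of a continuous predictor, say so separately and not as a comparison of the arms.

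Add that non-significant binary secondary outcomes will be interpreted through their 95% confidence intervals and not taken as evidence of no effect.

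The cost is one corrected sentence and one added line. No women are added and no design element changes; the published figure becomes less favourable.

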### Statistical analysis

Analysis will primarily be carried out according to the intention-to-treat principle, i.e., the participants will be analysed according to their randomized allocation, regardless of the actual interventions received by the participant. Supplementary, we will perform analyses per protocol, i.e., according to actual SSRI use, irrespective of randomized arm.

The primary outcome, risk (cumulative incidence up to 3 months postnatal) of relapse of depression, will be compared between the randomized groups. Differences will be assessed statistically using a one-sided Chi-Square Test at a significance level of .025 and will be presented as a risk difference. The remainder of statistical tests will be performed two-sided at a significance level of .05.

Time to relapse will be compared between the randomized groups using survival analysis. Kaplan-Meier curves will be constructed and differences will be tested using the log-rank test. A Cox proportional hazard model will be used to calculate hazard ratios

Continuous outcomes, e.g., the General Movements scores at 3 months, will be compared between the groups using the unpaired *t*-test. Categorical secondary outcomes, e.g., obstetric complications, will be tested using Chi-Square Tests. For the continuous variables and categorical variables that are assessed more than twice, we will deploy linear mixed models and generalized linear mixed models respectively. These models use all available data (do not exclude persons with missing values) under the assumption of data being missing at random, and account for within-subject correlation over time. If despite randomization prognostically important factors differ between the groups, they will be adjusted for in supplemental analyses by including these factors in the pertaining regression models.

Subgroup analyses will be undertaken according to: Dutch/non-Dutch, nulliparous/multiparous, yes/no history depressive disorder and/or anxiety disorder, yes/no co-morbid anxiety symptoms or disorder. All effect parameters will be supplied with a 95 % confidence interval.

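### The analysis called per protocol is an as-treated comparison by actual SSRI use; without a time rule for use, it is open to bias that likely favours stopping

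*Protocol article*

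**What the plan says.** The Statistical analysis section of the protocol article sets the primary approach: "Analysis will primarily be carried out according to the intention-to-treat principle". Relapse risk "will be compared between the randomized groups. Differences will be assessed statistically using a one-sided Chi-Square Test at a significance level of .025". It then adds: "Supplementary, we will perform analyses per protocol, i.e., according to actual SSRI use, irrespective of randomized arm".

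The Sample size section justifies the 15-point margin partly by "taking into account the possibility of restoring SSRI treatment", so restarting an SSRI is foreseen; no share is given. The Preventive cognitive therapy section provides the therapy in the discontinuation arm only. According to the Outcome measures section, medication use in both arms is monitored by telephone at 24 and 36 weeks of gestation and at 4 and 12 weeks postpartum. The article does not state at what time, or over what window, actual use is classified.

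**The concern.** A per-protocol analysis keeps women in the arm to which they were randomized and restricts to those who followed that arm's strategy. The analysis described here regroups everyone by SSRI use. This has three consequences.

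- **Randomization is lost.** Users and non-users may differ in prognosis, and the reason for using or not using an SSRI may itself be related to relapse.
- **Half of the intervention is ignored.** STOP is tapering plus cognitive therapy. A STOP woman who had the therapy but did not taper is pooled with GO women who had none.
- **The outcome may determine the group.** Relapse can lead to restart, and restart makes a woman a user.

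Non-adherence before relapse tends to pull an ITT difference towards zero, which favours a non-inferiority claim. A per-protocol analysis is the usual companion check. Here the only analysis carrying that name does not do the job, and may err in the same direction as ITT.

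**Working it through.** **1. The plan's own figure.** Inputs from Sample size: "We will use a non-inferiority margin (tolerance threshold, ‘delta’) of 15" per cent; "the assumption that the overall absolute risk of relapse will be around 15" per cent; "we need 178 women, given alpha .025, power 80 %, and a one-sided test".

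n per arm = (1.960 + 0.842)² × 2 × 0.15 × 0.85 / 0.15² = 88.95, rounded up to 89, so 178 in total. The stated figure is reproduced. The plan continues: "To account for some attrition, we aim to include 200 women in total"; 1 - 178/200 = 11% attrition. None of this depends on the point at issue.

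**2. When can use be classified?** Every participant uses an SSRI at entry, so simple ever-use cannot separate the groups; a later time is needed. Entry is before 16 weeks and the aim is to taper within four weeks. The first routine medication contact for both arms after entry is at 24 weeks. A STOP woman could therefore taper, relapse and restart before that contact, and would be recorded there as a user.

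**3. Expected effect of restart.** Assumptions: 100 women per arm; a share r of relapsed STOP women restart and are counted as users; everyone else follows allocation. The documents give no r, so the whole range is shown. With S relapses in STOP and G in GO:

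- users: (G + rS) / (100 + rS)
- non-users: (1 - r)S / (100 - rS)
- as-treated difference = non-users minus users

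Examples at r = 50%:

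- S = 15, G = 15: 7.5/92.5 - 22.5/107.5 = 8.1% - 20.9% = -12.8 points
- S = 30, G = 15: 15/85 - 30/115 = 17.6% - 26.1% = -8.4 points

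| r | true difference 0 (15% v 15%) | true difference +15 (30% v 15%) |
|---|---|---|
| 0% | 0.0 | +15.0 |
| 25% | -6.4 | +3.4 |
| 50% | -12.8 | -8.4 |
| 75% | -19.4 | -20.9 |
| 100% | -26.1 | -34.6 |

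**4. Chance of a false non-inferiority reading.** This was simulated at a true excess of 15 points (40,000 runs, 100 per arm, non-inferiority if the upper 95% limit with unpooled variance lies below 15 points). The as-treated comparison meets the criterion in about 2.5% of runs at r = 0, 50% at r = 25% and 98% at r = 50%. The randomized comparison stays near 2.5% throughout.

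**5. Other crossover.** Suppose also that 20% of STOP women never taper and 10% of GO women stop, unrelated to relapse and with risks kept as in the allocated arm. At a true +15 the as-treated difference is then +10.6, +1.2 and -8.5 for r = 0, 25% and 50%.

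The reverse flow acts the other way. If a share s of relapsing GO women leave their SSRI and count as non-users, then at a true +15:

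- r = 25%, s = 50%: 7.5 women move each way, giving 30/100 - 15/100 = +15.0
- r = 0, s = 25%: 33.75/103.75 - 11.25/96.25 = +20.8

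So restart always pushes towards stopping, but the net direction depends on flows in both arms.

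**The case against.** The strongest reply has four parts.

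**The time rule.** The article is silent on when use is classified, and the full protocol and analysis plan, where such a rule commonly sits, are not shown. Classification before relapse, or as time-varying, would remove the restart mechanism. This stands: a reader might infer that the analysis is certainly biased in favour of stopping, and the documents do not support that. They mention restart only as a possibility, give no share, and do not exclude offsetting crossover in GO.

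**The role of the analysis.** It is supplementary. The primary comparison is between randomized groups, and the economic evaluation branches on relapse incidence against the threshold without mentioning this analysis. This also stands and limits the severity.

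**The pragmatic design.** The trial compares strategies, and its margin was set with restoration of treatment in mind. Making agreement with a per-protocol result a condition of the non-inferiority claim would therefore be debatable, and it is not asked for here.

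**The value of actual exposure.** For child outcomes, actual exposure is of interest in itself; meconium and breast milk are collected to map it. The analysis by use need not be dropped.

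None of this rescues the label. The sentence itself equates per protocol with use regardless of arm. That is a wrong statement, not a detail left to another document.

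**Conclusion.** The point holds, at moderate severity. What the article calls per protocol is as-treated. It discards randomization, disregards the therapy component, and leaves no true per-protocol check beside ITT.

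The bias is conditional. If use is classified at or after relapse, restart by relapsed STOP women moves the result towards stopping. Under the illustration's assumptions (100 per arm, no other crossover), a quarter restarting is enough to shrink a true +15 to +3.4, and half restarting reverses its sign. That direction is likely rather than certain.

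A reader might go further and conclude that the analysis would confirm non-inferiority whenever stopping raises relapse by the full margin. The figures do not show that: it depends on the restart share, the time rule and crossover in GO. Nor is the trial's main conclusion compromised, since the primary ITT test and the sample size of 178 are untouched.

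**What to change.** - **Define the supplementary per-protocol analysis within randomized arms.** Judge adherence to the assigned strategy only up to SCID-confirmed relapse. A woman who relapses before finishing the taper or the sessions stays in, and SSRI changes after relapse do not alter membership. Restricting STOP to completers would not do, because it can drop early relapses and so favour stopping again.
- **Report it beside ITT**, as a risk difference with 95% confidence interval against the same 15-point margin.
- **Relabel the analysis by actual SSRI use as exploratory as-treated.** For the maternal outcome, treat use as time-varying before relapse. It may be kept for child exposure outcomes, with confounding acknowledged.

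The cost is wording in the protocol or analysis plan. Medication use and therapy adherence are already monitored; the timing of SSRI changes relative to relapse must be usable from those records. The set will be somewhat smaller and the interval wider. It remains a selected subset, which is why it supplements ITT and does not replace it.

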### Trial objectives

In this randomized controlled trial (RCT), the effect of preventive cognitive therapy (PCT) with guided tapering of SSRIs in early pregnancy will be compared to continuation of SSRIs during pregnancy. We will study effects on both mother and child with a pragmatic approach. The expectation is that tapering of SSRIs with added PCT does not increase the risk of clinically relevant maternal relapse or recurrence^1^ of depression or onset of anxiety disorders during pregnancy up to three months postpartum in excess of [absolute] 15 % compared to continuation of SSRIs. If so, discontinuation is deemed non-inferior with regard to relapse/recurrence risk. Furthermore, we expect that tapering of SSRIs is better than continuation of SSRIs with respect to child development. Finally, but not unimportantly, we hypothesize that discontinuation will decrease total costs per woman and child on a 3 months and projected long term base, assuming no relevant effects of discontinuation on the mother and no effects on the child are found.

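### The named primary test, a one-sided Chi-Square Test, ordinarily has an equal-risk null and does not use the 15-point margin on which the aim and the sample size rest

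*Protocol article*

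**What the plan says.** The aim and the margin are clear. Under Trial objectives, the expectation is that tapering with preventive cognitive therapy does not raise relapse risk "in excess of [absolute] 15 % compared to continuation of SSRIs", followed by: "If so, discontinuation is deemed non-inferior with regard to relapse/recurrence risk". Under Sample size: "We will use a non-inferiority margin (tolerance threshold, ‘delta’) of 15" per cent. The inputs there are "the assumption that the overall absolute risk of relapse will be around 15" per cent, and "we need 178 women, given alpha .025, power 80 %, and a one-sided test".

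Under Statistical analysis, the primary comparison is given in one sentence: "Differences will be assessed statistically using a one-sided Chi-Square Test at a significance level of .025", with the result presented as a risk difference. The section names no null hypothesis, margin, direction or decision rule. It uses the same test name for ordinary categorical secondary outcomes. It also promises a 95% confidence interval for every effect parameter.

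Economic evaluation is the only analysis text that ties a conclusion to the 15% threshold. Non-inferiority is confirmed if relapse incidence lies within it, and discontinuation is rejected as inferior if incidence is higher. It does not say whether this refers to the estimated difference or to its confidence limit.

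**The concern.** A chi-square test for two proportions asks whether the risks are equal. A non-inferiority trial asks whether the excess risk can be shown to be smaller than the margin. The two questions can have different answers in the same data, so the primary p-value as described does not settle the primary question.

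This is the trial's only primary decision. It concerns maternal relapse, the abstract says a positive result may make tapering the preferred strategy in pregnancy, and it selects the form of the economic analysis. An analyst who follows the sentence literally must improvise the step from p-value to conclusion, and some natural improvisations have poor error control.

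**Working it through.** **Inputs.** Margin 15 points absolute (Trial objectives, Sample size); relapse risk 15%, one-sided alpha .025, power 80%, 178 women (Sample size); 1:1 allocation and 200 women (Randomisation). Assumption: the 15% overall risk applies to each arm.

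**1. Reproduce the sample size with the margin in the null.**

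n per arm = (z₀.₉₇₅ + z₀.₈₀)² × [p(1−p) + p(1−p)] / δ² = (1.960 + 0.842)² × (2 × 0.15 × 0.85) / 0.15² = 7.849 × 0.255 / 0.0225 = 88.95, so 89 per arm and 178 in total. The match is exact.

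**2. Try the equal-risk chi-square instead** (one-sided .025, 80% power).
- 15% vs 30%: 242 women, or 268 with continuity correction.
- 7.5% vs 22.5%, if 15% is read as the average of the two arms: 176. Close, but not 178.

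The stated figure thus belongs to H0: risk(STOP) − risk(GO) ≥ 15 points.

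**3. Operating characteristics with GO risk 15%.** Each rate sums the product of two binomial probabilities over all pairs of relapse counts. The chi-square is uncorrected with cut-off 1.96.

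| Rule | True STOP risk | 89 per arm | 100 per arm |
|---|---|---|---|
| Chi-square significant for STOP lower | 15% | 2.4% | 2.6% |
| Chi-square significant for STOP lower | 10% | 16.9% | 18.8% |
| Chi-square not significant for STOP higher | 30% (at the margin) | 32.7% | 27.1% |
| Estimated difference below 15 points | 30% | 51.1% | 46.6% |
| Upper 95% Wald limit below 15 points | 15% | 80.1% | 84.3% |
| Upper 95% Wald limit below 15 points | 30% | 2.6% | 2.6% |
| Upper 95% Miettinen-Nurminen limit below 15 points | 15% | 78.9% | 82.8% |
| Upper 95% Miettinen-Nurminen limit below 15 points | 30% | 2.6% | 2.5% |

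Only the rules that set a confidence limit against the margin come close to the planned 80% power and 2.5% error.

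**4. Two data sets, 89 per arm (Wald intervals).**
- 23 (STOP) vs 13 (GO) relapses: difference 10/89 = 11.2 points, standard error 5.96 points, interval 11.2 ± 1.96 × 5.96, i.e. −0.4 to 22.9. The chi-square one-sided p is .031, so no significant excess, yet non-inferiority is not shown.
- 7 vs 1: difference 6/89 = 6.7 points, standard error 3.06 points, interval 0.7 to 12.7. The chi-square p is .015, a significant excess, yet non-inferiority is shown.

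Miettinen-Nurminen intervals (−0.6 to 23.1 and 0.8 to 14.4) give the same two conclusions. The second data set needs relapse risks far below the planned 15%. At a GO risk of 15% the realistic conflict is the first kind: a non-significant chi-square with the Wald limit not below 15 points occurs in 17.5% of trials at equal risks and in 30.1% at the margin.

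**The case against.** The best defence is that the sentence is incomplete rather than wrong. It gives no null, and its one-sided .025 level matches the margin-based sample size. Score tests with a shifted null exist and are of chi-square type, so the authors probably meant one. The risk difference and its 95% interval will be reported, and setting the upper limit against 15 points is exactly a one-sided .025 non-inferiority test. The article is also a condensed account, and the full protocol or analysis plan may say more.

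Much of this stands. The margin, the alpha, the sample size and the promised interval all fit a correct analysis. What does not stand is that the text already contains that analysis. It names a test, and by its ordinary meaning the wrong one. A misnamed primary test is not a detail left to another document. Nor does Economic evaluation repair it, because its wording also admits the point-estimate reading, which passes about half of trials at the margin.

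Two stronger readings are tempting and should be resisted. A reader might infer that the test can never establish non-inferiority. That is too strong, since a significant result favouring STOP implies it, though rarely under the design assumption. A reader might also take 2.4% and 33% as the plan's actual power and error rate. They belong to decision rules that the article does not adopt, and they show only what each way of using the named test would do.

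**Conclusion.** The concern holds as a mismatch between the named primary test and the trial's hypothesis. The sample size is sound and reproduces exactly. The test sentence does not use the margin, does not carry the stated 80% power, and is not joined to any rule that leads to a non-inferiority conclusion.

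The size of the problem depends on how the gap is filled. Setting the confidence limit against the margin costs nothing. Reading a non-significant excess as non-inferiority would raise the error at the margin from an intended 2.5% to about 33% (27% without attrition), and using the point estimate would raise it to about 51% (47%). These figures assume a GO risk of 15%, independent binomial outcomes, no missing outcomes and an uncorrected chi-square. With 7.5% vs 22.5% at the margin and 89 per arm, the first error rate would be 18.1%. The direction of the finding does not depend on these assumptions.

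**What to change.** In Statistical analysis, replace the test sentence with: *The risk difference (STOP minus GO) will be reported with a two-sided 95% score confidence interval (Miettinen-Nurminen). Non-inferiority is concluded if its upper limit is below +15 percentage points, equivalent to a one-sided .025 test of H0: difference ≥ 15 points.*

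In Economic evaluation, make the choice between the two analyses depend on that same rule, so that one criterion governs both sections. If a separate analysis plan already states such a rule, align the protocol text with it.

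The cost is two short text changes, made before the primary analysis. No extra patients or data are needed. With 89 per arm the Wald version has 80.1% power and the Miettinen-Nurminen version 78.9%; with all 200 women analysed they have 84.3% and 82.8%. No superiority test need be added.
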